### 5.3. Considerations Regarding Lifestyle

#### 5.3.1. Diet and Dietary Restrictions

No special restrictions.

#### 5.3.2. Caffeine, Alcohol, Tobacco, and Other Habits

No special restrictions.

#### 5.3.3. Physical Activity

If gas tamponade has been performed, the subject must not travel by air until the intra-ocular gas bubble has disappeared (because the gas bubble may expand and cause an increase in intra-ocular pressure). The subject should also avoid going to high altitudes or mountainous areas. Caution is also required with rapid ascent in elevators.

#### 5.3.4. Other Activities

If gas tamponade has been performed, the subject must not receive hyperbaric oxygen therapy until the intra-ocular gas bubble has disappeared.

#### 5.4. Screening Dropouts

Screening dropout occurs when a subject who has consented to participate in the clinical trial subsequently fails to meet any of the inclusion criteria or meets any of the exclusion criteria. To satisfy CONSORT reporting requirements and to respond to inquiries from regulatory authorities, minimal information (demographic characteristics and the reason for screening dropout) shall be recorded for subjects who are deemed ineligible at screening.

When medically and ethically appropriate, rescreening may be permitted for subjects who experienced screening dropout. If rescreening is performed, informed consent shall be obtained again and a new subject identification number shall be assigned.

#### 5.5. Criteria for Temporary Deferral of Enrollment

Not applicable.

### 6. Study Interventions and Concomitant Therapies

Study interventions refer to all pre-specified investigational products, non-investigational study drugs, medical devices, and other interventions (e.g., surgical or behavioral interventions) that are used or performed on subjects during the conduct of the trial.

#### 6.1. Procedures for Study Interventions

The study interventions to be administered are listed in Table 6-1, and the procedures for the study interventions are described in Table 6-2.

Table 6-1. Interventions to Be Performed

| Intervention Label | Monteplase (recombinant)                                                                                           | Vitrectomy | Gas tamponade※
1                                                                               | Silicone oil※1           |
|--------------------|--------------------------------------------------------------------------------------------------------------------|------------|---------------------------------------------------------------------------------------------------|--------------------------|
| Intervention Name  | Japanese name:
Monteplase (recombinant)
(JAN)
English name:
Monteplase (genetical recombination) (JAN) | Vitrectomy | Air, sulfur hexafluoride (SF 6 ) or octafluoropropane (C 3 F 8 ) | Silicone-oil replacement |
| Dosage Form /      | Injectable solution (vial)                                                                                         | —          | All are                                                                                           | colorless                |

|                           |                                                                                                                                                                                                                                                                                                                     |                    |                              |                             |
|---------------------------|---------------------------------------------------------------------------------------------------------------------------------------------------------------------------------------------------------------------------------------------------------------------------------------------------------------------|--------------------|------------------------------|-----------------------------|
| Physical Characteristics  | clear, colorless liquid                                                                                                                                                                                                                                                                                             |                    | colorless and odorless gases | liquid                      |
| Specification             | One vial (5 mL) containing 400,000 International Units (IU)                                                                                                                                                                                                                                                         | —                  | —                            | —                           |
| Dosage and Administration | Add 5 mL of physiological saline to one vial of monteplase (recombinant), dissolve completely without foaming to obtain a solution of 80,000 IU/mL; administer 0.1 mL (8,000 IU) sub-retinally after vitrectomy. If injection is difficult, the surgeon may, at his/her discretion, reduce the dose as appropriate. | —                  | Intra-ocular injection       | Intra-ocular injection      |
| Administration Frequency  | Once                                                                                                                                                                                                                                                                                                                | Once               | Once                         | Once                        |
| Route of Administration   | Sub-retinal administration                                                                                                                                                                                                                                                                                          | —                  | Intravitreal administration  | Intravitreal administration |
| Purpose                   | Investigational product                                                                                                                                                                                                                                                                                             | Adjunctive surgery | Tamponade                    | Tamponade                   |
| Packaging and Labeling    | 
Provided with the following information:
 
1) Indication that it is for clinical-trial use
 
2) Name and address of the clinical-trial coordinating physician
 
3) Chemical name or identifier
 
4) Batch number or
                                                                      | —                  | —                            | —                           |

|         |                                                                                                              |   |  |  |
|---------|--------------------------------------------------------------------------------------------------------------|---|--|--|
|         | manufacturing code
5) Storage conditions and
expiration date                                           |   |  |  |
| Storage | Store at room temperature
(1 – 30 °C) (room
temperature according to
the Japanese
Pharmacopoeia) | — |  |  |

※1 Select one.

Table 6-2

| Study-Arm Title        | Active Drug Group                                                                                                                                                                                                                                                                                                                                                                                                                                                                                                                                                                                                                                                                                                                                                                                                                                                                                                                                                                                                                                                                                                                                                                                                                                                                                                                                                       |
|------------------------|-------------------------------------------------------------------------------------------------------------------------------------------------------------------------------------------------------------------------------------------------------------------------------------------------------------------------------------------------------------------------------------------------------------------------------------------------------------------------------------------------------------------------------------------------------------------------------------------------------------------------------------------------------------------------------------------------------------------------------------------------------------------------------------------------------------------------------------------------------------------------------------------------------------------------------------------------------------------------------------------------------------------------------------------------------------------------------------------------------------------------------------------------------------------------------------------------------------------------------------------------------------------------------------------------------------------------------------------------------------------------|
| Intervention procedure | 
1) Perform local anesthesia or general anesthesia.
 
2) Conduct pars plana vitrectomy using a 3-port system with 23, 25 or 27-gauge instrumentation.
 
3) Phacoemulsification and intraocular lens implantation shall be performed at the discretion of the surgeon and according to the subject's preference.
 
4) Peeling of epiretinal membrane over the macula and internal limiting membrane is permitted.
 
5) Montepulse (recombinant) shall be administered with a sub-retinal injection needle into the sub-retinal hemorrhagic area located away from the fovea. Injection under the RPE and areas with RPE detachment shall be avoided to prevent RPE rupture. Multiple injection sites may be used as needed. During injection, intra-ocular pressure shall be monitored by palpation.
 
6) If retinal breaks are present, treat them with laser photocoagulation or cryotherapy.
 
7) Perform gas tamponade or silicone-oil exchange (the surgeon shall select either method based on the subject's severity, feasibility of positioning restrictions, etc.).
 
8) After montepulse (recombinant) administration, the subject shall remain in a supine or prone position for 20–60 minutes (including intra-operative time) according to the extent of hemorrhage. Thereafter, positioning restrictions shall be
 |

|                             |                                                                                                |
|-----------------------------|------------------------------------------------------------------------------------------------|
|                             | applied as directed by the surgeon, and the details shall be recorded in the case report form. |
| Related Intervention Labels | Monteplase (recombinant), vitrectomy, gas tamponade or silicone-oil exchange                   |

#### 6.1.1. Rescue Treatment

If the principal investigator or sub-investigator determines that it is necessary, the following treatments may be administered.

- ✓ VEGF inhibitor
- ✓ Intravitreal gas injection
- ✓ Photodynamic therapy

#### 6.2. Preparation, Handling, Storage, and Management

1) The investigational product may be administered only to subjects, and only the principal investigator, sub-investigator, or other personnel pre-designated in advance may prepare and administer the investigational product.

2) Procedures and records concerning receipt, inventory entry, dispensing, and disposal of the investigational product shall be performed in accordance with the separately defined “Standard Operating Procedure for Investigational Product Management.”

#### 6.3. Allocation of Trial Intervention

The principal investigator or sub-investigator shall, after obtaining written informed consent from the patient, confirm that all inclusion criteria are met and that none of the exclusion criteria apply. Thereafter, the principal investigator, sub-investigator, or clinical research coordinator will perform registration using an electronic data capture (EDC) system. All registered subjects will be assigned to the active-drug group.

[EDC System]

Fountainyn

Registration hours: 24-hour registration possible (excluding maintenance/inspection periods)

Contact: Kyushu University Hospital ARO Next-Generation Medical Center, Clinical Research Management Division, Data Science Office

Weekdays 9:00 – 17:00 (excluding Saturdays, Sundays, public holidays, and the year-end/New-Year period (12/29 – 1/3))

Precautions for registration:

- ✓ Registration after administration of montepase (recombinant) is not permitted under any circumstances.
- ✓ In the EDC system, registration will not be accepted until all required input fields are completed.
- ✓ Registration is considered complete when eligibility is confirmed and a registration number is issued.
- ✓ Except when a subject withdraws consent, including refusal to allow data use, a subject once registered will not have that registration cancelled. In the event of duplicate registration, the information from the first registration (including registration number) will be used.
- ✓ If erroneous or duplicate registration is discovered, the data-management staff must be notified promptly.

#### 6.4. Blinding

No blinding will be performed.

#### 6.5. Compliance with Trial Intervention

Under medical management, the subject shall receive the trial intervention from the principal investigator, sub-investigator, or a pre-designated responsible individual. The date of intervention, the eye receiving montepase (recombinant), the administered dose, the injection site, the details of positional restriction, and, if the dose is reduced or increased from the stipulated amount (0.1 mL), the reason shall be recorded; for gas tamponade or silicone oil exchange, the material used shall be recorded.

#### 6.6. Dose Adjustment of Trial Intervention

If, based on the extent of hemorrhage or retinal condition, sub-retinal administration of 0.1 mL is judged to be difficult (e.g., investigational product spreading beyond the retinal vascular arcade) by the principal investigator or sub-investigator, the dose may be reduced as appropriate. Furthermore, after Visit 1, no additional sub-retinal administrations shall be performed except in cases of re-bleeding.

#### 6.7. Continuation of Trial Intervention After Trial Completion

No specific treatment after completion of this study will be stipulated. However, for subjects who provide consent to participate in an observational study for long-term visual prognosis, ophthalmologic examination results will continue to be collected after completion of the study.

#### 6.8. Treatment of Overdose

Administration of recombinant alteplase exceeding 8,000 IU shall be considered an overdose. In the event of an overdose, the principal investigator or sub-investigator shall take the following actions:

- 1) Observe the subject's condition and provide medically necessary interventions.
- 2) Carefully monitor the subject for any adverse events and any abnormal clinical laboratory values.
- 3) Record the amount of the overdose and report it, together with the subject's condition, to the trial-coordinating physician.
- 4) Document the reason for the overdose and the administered dose in the case report form.

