|                                                                                 | Intravenous, sub-retinal, or intravitreal administration of tPA preparations other than alteplase (recombinant) | Additional treatment for SMH                                                                                      | Virtual                        | Virtual                        | Virtual                         | Virtual                                          | Virtual                        | Virtual            | Virtual                         | Virtual                                                                   |
|                                                                                 |                                                                                                                 | Treatment of other diseases (acute myocardial infarction, cerebral infarction)                                    | Treatment policy               | Treatment policy               | Treatment policy                | Treatment policy                                 | Treatment policy               | Treatment policy   | Treatment policy                | Treatment policy                                                          |
|                                                                                 | Intravenous or intravitreal administration of alteplase (recombinant)                                           | Additional treatment for SMH                                                                                      | Virtual                        | Virtual                        | Virtual                         | Virtual                                          | Virtual                        | Virtual            | Virtual                         | Virtual                                                                   |

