|                                                                                 |                                                                                                                 | Treatment of other diseases (acute myocardial infarction, acute pulmonary embolism)                               | Treatment policy               | Treatment policy               | Treatment policy                | Treatment policy                                 | Treatment policy               | Treatment policy   | Treatment policy                | Treatment policy                                                          |
|                                                                                 | Hemorrhage removal surgery                                                                                      | Additional treatment for SMH                                                                                      | Composite variable             | Composite variable             | Composite variable              | Composite variable                               | Composite variable             | Composite variable | Composite variable              | Composite variable                                                        |

§Including cases in which a tPA formulation (including alteplase (recombinant)) is administered via subretinal injection.

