##### 6.9.2. Concomitant Medication / Concomitant Therapy

###### 6.9.2.1. Prohibited Medications / Prohibited Therapies

The following are prohibited during the study period:

- 1) Defibrinated sodium (Defaterio).
- 2) Intravenous, sub-retinal, or intravitreal administration of tPA products other than alteplase (recombinant).
- 3) Intravenous or intravitreal administration of alteplase (recombinant).
- 4) Ophthalmic surgeries not listed in 6.9.2.2.

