###### 6.9.2.2. Permitted Medications / Permitted Therapies

The following surgical treatments or drug uses are permitted:

- 1) Phacoemulsification cataract extraction and intra-ocular lens implantation.
- 2) Epiretinal membrane and internal limiting membrane peeling.

- 3) Retinal photocoagulation or cryotherapy for retinal tears.
- 4) Antiplatelet agents (including agents with platelet-aggregation-inhibiting activity) and anticoagulants.

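### Sections 6.8 and 6.9.2.1 and Table 3-1 name alteplase where monteplase is meant, so the overdose rule misses the trial drug and the prohibited list bars the repeat dose that 6.6 allows

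*Protocol*

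**What the plan says.** The investigational product is monteplase throughout the title, objectives, dose rationale (4.3) and intervention table (Table 6-1). Four places use a different drug name in an operative rule:

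- **6.8:** "Administration of recombinant alteplase exceeding 8,000 IU shall be considered an overdose".
- **6.9.2.1 item 2** prohibits: "Intravenous, sub-retinal, or intravitreal administration of tPA products other than alteplase (recombinant".
- **6.9.2.1 item 3** prohibits: "Intravenous or intravitreal administration of alteplase (recombinant".
- **Table 3-1** has one row for "tPA preparations other than alteplase (recombinant", a second row for intravenous or intravitreal alteplase, and a footnote to the re-bleeding row: "Including cases in which a tPA formulation (including alteplase (recombinant)) is administered via subretinal injection".

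Two further provisions bear on the repeat dose. Section 6.6 rules out further sub-retinal dosing after Visit 1 but excepts re-bleeding, and 8.2.7 sets out what to record when that happens. Against this, 6.9.2.1 item 4 prohibits "Ophthalmic surgeries not listed in 6.9.2.2". The list it points to, which opens "The following surgical treatments or drug uses are permitted", names cataract surgery with lens implantation, membrane peeling, treatment of retinal tears, and antiplatelet and anticoagulant drugs. It does not name vitreous re-operation.

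**The concern.** Alteplase has no role in this trial. If the wording is followed as it stands, two rules fail.

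1. **Overdose.** The observation, monitoring, reporting and documentation steps in 6.8 are tied to a drug nobody will receive. Doses above 8,000 IU are foreseen: 6.5 asks for the reason when the dose is increased, and 9.7.2 has a subgroup above 8,000 IU. Section 10.2.1 keeps overdose itself out of AE and SAE reporting, except intentional self-harm. That leaves 6.8 as the only rule that sends an overdose as such to the trial-coordinating physician.
2. **Repeat dose.** Monteplase is a tPA product other than alteplase, so item 2 prohibits giving it sub-retinally, with no exception. A site that follows 6.6 would have to log a prohibited drug (item 2) and, on the wording of item 4, a prohibited surgery.

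The same slip reaches the estimand. A monteplase re-dose at re-operation for re-bleeding falls under the composite strategy through the footnote, and literally also under the hypothetical strategy (called virtual in the table) in the row for other tPA given as additional treatment for SMH.

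**Working it through.** **Count of the name.** Section 2.2 uses it once, for the product of a European trial, and that use is correct. Section 6.8 uses it once, 6.9.2.1 twice (items 2 and 3), and Table 3-1 three times (two rows and the footnote). The total is 1 + 1 + 2 + 3 = 7, of which 6 are wrong.

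**Which drug was meant.** The protocol answers this itself:

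- *Dose.* Table 6-1 gives 400,000 IU in 5 mL, so 400,000 / 5 = 80,000 IU/mL, and 80,000 × 0.1 mL = 8,000 IU. The threshold in 6.8 is exactly the monteplase dose.
- *Indications.* The alteplase row of Table 3-1 lists "Treatment of other diseases (acute myocardial infarction, acute pulmonary embolism"). Section 2 gives these two as the approved Japanese indications of monteplase.
- *Route.* Item 3 leaves out the sub-retinal route, which makes sense only for the trial drug.
- *Parallel text.* Section 9.3.2 describes the same prohibited tPA events and names monteplase.

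**What the name correction repairs.** With monteplase in place, item 2 bars other tPA by all three routes, and item 3 bars monteplase by the intravenous and intravitreal routes. Sub-retinal monteplase is then no longer prohibited as a drug. Item 4 still stands in the way of the surgery needed to give it. Another tPA given sub-retinally at re-bleeding would still fit both the composite footnote and the hypothetical row.

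**Effect on the primary analysis.** Section 9.3.2 imputes a change of 0 for re-surgery due to re-bleeding. The literal Table 3-1 row would instead exclude the data. The number of such subjects before Week 1 is not given, so k = 0 to 2 of 20 is assumed. The other subjects are set at the 9.9 planning values (mean −120 µm, SD 170 µm), and excluded values are not imputed (9.1.4).

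For change = 0 with n = 20:

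- mean = (20 − k)(−120)/20
- SD = √{[(19 − k)·170² + (20 − k)·(k/20)·120²]/19}
- t = mean/(SD/√20), 19 df

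For exclusion: n = 20 − k, t = −120/(170/√n), n − 1 df.

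| k | Change = 0: mean, SD | t, two-sided p | Excluded: mean, n | t, two-sided p |
|---|---|---|---|---|
| 0 | −120.0, 170.0 | −3.16, 0.0052 | −120, 20 | −3.16, 0.0052 |
| 1 | −114.0, 167.6 | −3.04, 0.0067 | −120, 19 | −3.08, 0.0065 |
| 2 | −108.0, 165.0 | −2.93, 0.0086 | −120, 18 | −2.99, 0.0081 |

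For k = 1 the SD is √[(18 × 28,900 + 0.95 × 14,400)/19] = √28,099 = 167.6.

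**Sample size.** An exact one-sample t-test with effect size 0.7, two-sided 5% and 80% power gives n = 19 (power 82.3%; 79.9% at n = 18), and 19/0.95 = 20. Both match 9.9 and are untouched by this point.

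**The case against.** The strongest reply is that no site would read the text this way. Section 6 deals with one thrombolytic, the threshold matches its dose, and 6.6 is the more specific clause on re-dosing. Read strictly, item 2 would bar even the Visit 1 dose, an absurd result that shows the literal reading is not the working one. There are backstops: 6.5 records the dose and the reason for any increase, and sequelae of an overdose are adverse events. Some of the six wrong uses also have little effect. The footnote says including, so it already covers monteplase. For intravenous and intravitreal use the two Table 3-1 tPA rows carry the same strategies, so swapping the names changes nothing there. Table 3-1 keeps vitreous re-operation outside its prohibited-therapy block, which suggests the authors did not regard it as prohibited. Other drug names are misspelled in the text, so this may be a translation slip.

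Most of this stands as mitigation. It limits the practical harm and rules out a higher rating. It does not make the rules right. An overdose without sequelae reaches the trial-coordinating physician only through 6.8. Item 2 contains no exception, and item 4 is a separate obstacle whatever Table 3-1 implies. Whether a source-language version names the drug correctly cannot be seen here.

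**Conclusion.** The concern holds and should be fixed. Six of seven uses of alteplase are wrong, and they sit in a safety rule, a prohibited-therapy list and the intercurrent-event table. As written, the 6.8 overdose rule does not apply to monteplase, and 6.9.2.1 items 2 and 4 bar the re-dose and re-operation that 6.6 and 8.2.7 foresee.

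The statistical effect is minor. No sample-size figure or test conclusion changes. The gap between the two readings of Table 3-1 is 6 µm in the mean with one affected subject and 12 µm with two, and none if there are no such subjects. Those figures rest on the assumed count of 0 to 2 and on the planning mean and SD. Confidence in the misnaming is high, because the dose, indications, route and parallel text all point to monteplase.

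**What to change.** - Replace alteplase with monteplase in 6.8, in 6.9.2.1 items 2 and 3, and in the two Table 3-1 tPA rows and the footnote.
- Add vitreous re-operation with sub-retinal monteplase for re-bleeding to 6.9.2.2, or except it from 6.9.2.1 item 4, so that the repeat dose in 6.6 is actually permitted.
- State under Table 3-1 that the re-bleeding footnote takes precedence over the rows for additional treatment of SMH. This also settles the case of another tPA given sub-retinally at re-bleeding, which the name correction alone does not.

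The cost is six word replacements, one added line or exception, and one note under the table, at the next protocol amendment. Site documents and EDC labels are not visible here and should be checked for the same name.
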